**Methods:**

Sixty older adults (≥60 years of age) with mild to moderate depression will be randomly assigned to an experimental or a control condition. The participants in the experiment group will receive the reminiscence therapy under the Watt’s protocol with adaptation to Chinese Culture which consists of six weekly sessions of 90 minutes each. The control group will be treated as before. An assessor who is blind to intervention will conduct the measures before treatment, after treatment immediately, and three months after treatment.

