In the last several decades, increasing studies indicated that reminiscence therapy is effective for the elderly with depression [26,28-33]. Besides alleviating the depression symptoms, reminiscence therapy was proved to improve self-esteem [34], life satisfaction [35], psychological well-being [36], personal mastery [37,38] and loneliness [39,40]. However, the conclusion is not consistent [41-43]. The reasons may be attributed as some studies did not follow randomized controlled trial (RCT) design, lack of strict protocol and had high dropout rates.

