## Method

### Design

The trial will be conducted as a pre-post test compared and randomized controlled trial. After collection of the baseline test, research assistant will open a sealed sequential randomization envelope for each participant indicating either the “reminiscence therapy group” or the “waiting-list control group”. The envelopes have been prepared previously by the evaluator via a computerized randomized program. The assessments will be conducted by another evaluator who is not the therapist and is blind to the group assignment.

The reminiscence therapy group participants will receive six-week interventions, while the control group participants will not receive any emotional related treatment. After the intervention, all the participants will receive post-test. Then after three months, all the participants will receive the follow-up test. An overview of the study design is shown in Figure 1.

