### Participants

A total of sixty subjects who fulfill the following inclusion and exclusion criteria will be recruited from the community.

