### Statistical analysis

According to some previous researches, personal characteristics of the subjects may have an impact on the outcomes. Though the RCT design is adopted, the demographic data between the control group and the experiment group still should be considered. When the two groups do not match on demographic data, related statistical methods will be brought in to make up for this. In addition, the data of participants who are absent from the group session for four times or more and who turn to antidepressant or other non-pharmaceutical intervention before the end of the therapy will be excluded when analyses conducted [39].

SPSS 16.0 statistical packages will be used to conduct the data analyses. Paired *t* test will be used to detect the changes of the outcome measures within intervention or control group. Standardized change scores will be calculated by subtracting pre-test score from post-test score of intervention and dividing by the SD for all participants combined. A repeated measures analysis of covariance (ANCOVA) model will be used to evaluate the effects of intervention on continuous outcome variables that are available at each data collection point. The between-subjects factor is group (intervention group, control group) and the within-subjects factor is assessment phase (baseline, post-test, follow-up test). All statistical tests were two sided, and *p* values < 0.05 were considered significant. In addition, effect sizes (Cohen’s d) [52] will be computed based on the differences between the pre-and post-intervention (or follow-up test) means and the pooled variance.

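### The only between-group test, a three-phase repeated measures ANCOVA, in its classical form drops participants who miss just the three-month visit from the post-test comparison

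*Protocol article*

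**What the plan says.** In the protocol article, the Statistical analysis section sets out these analyses:

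- A repeated measures ANCOVA to evaluate the "effects of intervention on continuous outcome variables that are available at each data collection point". Group is the between-subjects factor, and "the within-subjects factor is assessment phase (baseline, post-test, follow-up test"). This is the only test that compares the arms.
- Paired t tests of change within each arm, standardized pre-to-post change scores, and Cohen's d for pre to post or pre to follow-up.
- Software: "SPSS 16.0 statistical packages will be used to conduct the data analyses".
- Error rate: "All statistical tests were two sided, and *p* values < 0.05 were considered significant".

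The section mentions neither imputation nor a mixed model, and it has no separate between-group analysis of the post-test. It also does not say in words that participants with a missed visit are removed.

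On aims and follow-up, Study purposes asks first for the group difference after six weeks of therapy and then whether it is maintained to three months. Design expects full attendance: "Then after three months, all the participants will receive the follow-up test". The Background, under Reminiscence therapy, suggests that earlier results may be inconsistent because "some studies did not follow randomized controlled trial (RCT) design, lack of strict protocol and had high dropout rates".

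**The concern.** A classical repeated measures ANCOVA treats a participant's three scores as one record. If one score is missing, the whole record is unusable. The later and more fragile visit therefore decides who counts in the earlier comparison.

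Two things are at stake. First, observed post-test scores on the primary outcome are thrown away in a trial of only 60 people. Second, those who attend all three visits are a selected group. One arm attends weekly group therapy and the other waits, so the reasons for missing the last visit may differ between arms. If they differ in a way linked to the post-test score, the six-week contrast among completers no longer estimates the contrast in those randomised. Some loss is foreseeable: the article cites dropout as a weakness of earlier studies and allows withdrawal at any time.

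**Working it through.** The article states no power, effect size, SD, correlation or dropout rate, so there is no planned figure to reproduce.

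**Inputs from the article**
- Sample size 60 (Participants): "A total of sixty subjects who fulfill the following inclusion and exclusion criteria will be recruited from the community".
- Two arms (Abstract, Methods): participants "will be randomly assigned to an experimental or a control condition". The ratio is not stated.
- Two-sided 5% level and three phases (Statistical analysis).

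**Assumptions**
- Equal arms.
- True post-test effect 0.6 SD.
- Baseline to post-test correlation r = 0.5.
- Loss of 10%, 20% or 30% at the three-month visit only, with every post-test observed.

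**Step 1: who remains.** Three-visit completers = 60 × (1 − loss), which gives 54, 48 and 42. The post-test scores discarded although observed number 6, 12 and 18.

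**Step 2: power of the plan's post-test contrast.** Baseline is a level of the phase factor, so the relevant contrast is the group difference in change from baseline to post-test. In SD units of the raw score:

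- SD of change = √(2(1 − r)) = √(2 × 0.5) = 1.
- Noncentrality = 0.6 / (1 × √(2/n)), with n per arm.
- Power from the noncentral t distribution with 2n − 2 degrees of freedom.

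| Analysed (per arm) | Noncentrality | Power |
|---|---|---|
| 60 (30) | 2.32 | 63% |
| 54 (27) | 2.20 | 58% |
| 48 (24) | 2.08 | 53% |
| 42 (21) | 1.94 | 48% |

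The correlation matters. With r = 0.3, power is 49% at 60 and 41% at 48 (rounded). With r = 0.7 it is 84% and 75%. The drop from 60 to 48 is about 8 to 10 percentage points throughout.

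**Step 3: power with baseline as a covariate, for comparison.** The residual variance becomes 1 − r² = 0.75. With 2n − 3 degrees of freedom, power is 75% at 60, 65% at 48 and 59% at 42. These figures belong to a different model from the one planned. They are relevant to the remedy, not to the starting point.

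**Step 4: bias.** A large-sample simulation used a true post-test effect of −0.50 SD, correlations of 0.5 to 0.6 between visits and 20% follow-up loss in each arm. Where loss depended on the post-test score, it did so at 1 log-odds per SD. The difference in change among three-visit completers was:

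| How follow-up loss arises | Completer estimate |
|---|---|
| At random | −0.50 |
| Depends on post-test score, equally in both arms | −0.50 |
| Depends on post-test score in the therapy arm only | −0.56 |
| Opposite directions in the two arms | −0.64 |

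In the last two rows, participants with worse scores leave the therapy arm, so the error favours therapy. Reversing that pattern would reverse the sign.

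**The case against.** **Deletion is inferred, not stated.** This is correct. It follows from the classical form of the named model. Imputing first, or fitting the model by likelihood as a mixed model, would avoid it. An analysis plan that is not shown may do either, and silence on missing data in a condensed article is not in itself a fault. The point that stands concerns what the article does fix: the model, its three-level factor and the software. A plan that follows that text literally inherits the complete-case restriction.

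**The phrase about availability describes variables.** Also correct. "effects of intervention on continuous outcome variables that are available at each data collection point" most naturally separates scales given at every visit from those that are not. A reader might take it as a rule restricting the analysis to participants with complete data, but the wording does not support that. The three-level within-subjects factor carries the argument.

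**Other analyses keep these participants.** A reader might infer that someone who misses the last visit disappears from every analysis. That is not so. The paired t tests, the standardized change scores and the pre-post Cohen's d need only two visits. None of them, however, is a planned test of one arm against the other.

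**Bias is not inevitable.** This stands. With random loss, or loss linked to the score equally in both arms, the completer estimate in the simulation was not moved. Nothing in the article says that loss will depend on arm or on the post-test score, and dropout is only one of three suggested reasons for earlier inconsistency. The exclusion of people who cannot guarantee weekly attendance may also reduce loss somewhat, although it concerns sessions rather than the follow-up visit.

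**Conclusion.** The concern holds in a limited form. As written, and if fitted classically without imputation, the sole between-group test leaves out of the randomised six-week comparison anyone who misses only the three-month visit, even though the post-test score was observed. The loss of data is certain whenever such participants exist. Bias is possible, and requires follow-up loss that relates to the post-test score differently in the two arms.

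The size depends on a dropout rate that the article does not give. Under the stated assumptions, 10% to 30% follow-up-only loss takes power for the post-test contrast from about 63% to between 58% and 48%. With no loss at follow-up the problem vanishes. The document does not support the stronger conclusions that participants are deleted by rule, that they leave all analyses, or that both time points are necessarily biased. This is a change that should be made, because it affects the primary comparison and is easy to make.

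**What to change.** Replace the repeated measures ANCOVA with a likelihood-based linear mixed model, using the MIXED procedure in SPSS:

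- Data: all available post-test and follow-up scores of randomised participants.
- Terms: baseline score as covariate, group, phase (post-test, follow-up) and group by phase.
- Covariance: unstructured over the two post-baseline visits.
- Report: the group contrast at post-test and at three months separately.

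A participant with only a post-test score then contributes to the six-week contrast, and the model is valid when loss depends on observed scores. If all 60 have a post-test, the covariate-adjusted post-test contrast has about 75% power under the same assumptions. Part of that gain over the planned model comes from using baseline as a covariate, and part from keeping the observed data.

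If a mixed model or prior imputation was already intended, one sentence saying so would settle the point. A sensitivity analysis that worsens missing therapy-arm scores by a stated number of points is optional.

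The cost is revised wording and slightly more analysis work. No extra visits, data or participants are needed.

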### Study purposes

The purpose of the research is to examine the effect of reminiscence therapy on depressive symptom, self-esteem, life satisfaction, and loneliness in Chinese elderly.

Specifically, the aims are:

Firstly, we intend to explore whether reminiscence therapy will significant improve the experiment group’s depressive symptom in comparison with control group after six weeks therapy, and whether the efficacy can be maintained during three-month follow-up.

Secondly, we are interested in whether reminiscence therapy is a potential effective treatment to reduce the loneliness, increase the self-esteem and life satisfaction for the experiment group elderly.

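### Baseline is analysed as one of three outcome levels instead of as a covariate, so neither treatment test in the model matches the trial's two aims, and power is lost unless the visits are highly correlated

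*Protocol article*

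**What the plan says.** All references are to the protocol article.

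- **Model (Statistical analysis).** "A repeated measures analysis of covariance (ANCOVA) model will be used to evaluate the effects of intervention on continuous outcome variables". The factors are then fixed: "The between-subjects factor is group (intervention group, control group") and "the within-subjects factor is assessment phase (baseline, post-test, follow-up test"). No covariate is named. The only adjustment mentioned is for demographic data, and only if the groups do not match.
- **Significance (Statistical analysis).** "All statistical tests were two sided", and p "values < 0.05 were considered significant". The section does not say which F-test from the model decides.
- **Timing of baseline (Design).** "After collection of the baseline test, research assistant will open a sealed sequential randomization envelope for each participant". Baseline therefore precedes allocation.
- **Aims (Study purposes).** Depressive symptoms are to be compared "in comparison with control group after six weeks therapy, and whether the efficacy can be maintained during three-month follow-up". These are two questions, each tied to one visit.
- **Size (Participants).** "A total of sixty subjects who fulfill the following inclusion and exclusion criteria will be recruited from the community".

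**The concern.** Because baseline is taken before the envelope is opened, the groups differ there only by chance. Treating it as an outcome level means treatment has to be read from one of two F-tests:

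- The **group main effect** averages a time point that treatment cannot have affected with two that it can.
- The **group-by-phase interaction** asks whether the group difference varies over three phases. A significant result does not say whether the groups differ at post-test, at follow-up or at both.

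The baseline score is already collected. As a covariate it would reduce the residual variance and allow a single 1-df comparison at the visit named in the first aim. With 60 participants there is little power to spare, and the test that decides success should be clear before the data are seen.

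**Working it through.** The article gives no effect size, SD or power calculation, so there is no stated figure to reproduce.

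**Inputs**

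- From the article: 60 participants, two-sided 0.05, two groups, three phases, baseline before randomisation.
- Assumed: 1:1 allocation (n = 30 per arm; the ratio is not stated), no losses, equal variances and equal correlation r between visits (compound symmetry), and a true effect of 0.5 SD at post-test.
- Range for r: 0.3 to 0.8. The article gives no correlation for the trial's intervals. Its retest figures are 0.85 over one week for the GDS and 0.73 over twelve months for the UCLA scale in the elderly.

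**Step 1: what the main effect estimates.** Let d1 and d2 be the effects at post-test and follow-up. The main effect estimates (0 + d1 + d2)/3. The mean post-treatment effect is (d1 + d2)/2. The ratio is 2/3 for any d1 and d2, so a sustained 0.50 SD becomes 0.333 SD. This does not apply to the interaction.

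**Step 2: noncentrality (lambda) of each test**

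- Main effect: (n/2) × [(d1 + d2)/3]² / [(1 + 2r)/3], df 1, 58.
- Interaction: (n/2) × Σ(d_t − d̄)² / (1 − r), df 2, 116.
- ANCOVA at post-test with baseline as covariate: (n/2) × d1² / (1 − r²), df 1, 57.

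**Worked example, r = 0.5, sustained 0.5 SD**

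- Main effect: 15 × 0.1111 / 0.6667 = 2.5, power 34%.
- Interaction: the effects 0, 0.5, 0.5 have mean 0.333 and sum of squared deviations 0.1667. Lambda is 15 × 0.1667 / 0.5 = 5.0, power 49%.
- ANCOVA at post-test: 15 × 0.25 / 0.75 = 5.0, power 59%.

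At r = 0.5 the last two lambdas are equal, so the 10-point gain comes from using one degree of freedom instead of two. The ratio of the ANCOVA lambda to the interaction lambda is 1.5/(1 + r). It falls below 1 once r exceeds 0.5, which is why the gain shrinks as r rises.

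**Power, sustained effect (0.5 SD at both visits)**

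| r | Main effect | Interaction | ANCOVA, post-test | Gain over interaction (points) |
|---|---|---|---|---|
| 0.3 | 41% | 37% | 51% | 15 |
| 0.5 | 34% | 49% | 59% | 10 |
| 0.6 | 32% | 59% | 66% | 7 |
| 0.7 | 30% | 72% | 76% | 4 |
| 0.8 | 28% | 89% | 89% | 0 |

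**Power, fading effect (0.5 SD at post-test, 0.25 SD at follow-up)**

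| r | Main effect | Interaction | ANCOVA, post-test | Gain over interaction (points) |
|---|---|---|---|---|
| 0.3 | 26% | 28% | 51% | 23 |
| 0.5 | 22% | 38% | 59% | 21 |
| 0.7 | 19% | 59% | 76% | 17 |
| 0.8 | 18% | 78% | 89% | 11 |

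Gains are differences of unrounded powers.

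**Step 3: false positives if either F-test counted as success.** Treating the two tests as independent under the null, 1 − 0.95² = 9.75%. Simulation with 10,000 runs gave 9.7 to 10.0% for r from 0.3 to 0.7.

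**The case against.** The strongest defence is that, with baseline among the phases, the natural test of treatment is the interaction: do the groups change differently? The aims and the pre-to-post effect sizes in the Statistical analysis section point that way. The interaction is valid, the one-third loss does not touch it, and its power approaches that of ANCOVA when the visits are highly correlated. At r = 0.85 it is slightly ahead for a sustained effect (96% against 95%). The article is also condensed, so a fuller plan may list covariates and name the deciding test.

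Most of this stands, and it rules out several stronger readings that a reader might infer:

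- **The plan underestimates the treatment effect by one third.** This holds only for the group main effect, and the article never says that this test decides.
- **The analysis is biased or invalid.** It is not. The interaction is a proper test of differential change.
- **The fix raises power from 49% to 77% at r = 0.5.** The 77% belongs to ANCOVA on the mean of the two post-treatment visits. The first aim concerns post-test, where the like-for-like figure is 59%.
- **The trial runs a 10% false-positive rate.** That requires accepting either F-test as success, which the article does not say.

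What the defence does not remove is that placing baseline among the outcome levels is a stated choice, not a gap left to another document. Covariates listed elsewhere would not change that, because the baseline score cannot usefully serve as covariate while it is also a level of the outcome. Nor does the interaction alone locate a difference at post-test or at follow-up.

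**Conclusion.** The point holds as one of efficiency and fit to the aims. The stated model offers two treatment tests. The main effect has low power in both scenarios. The interaction is valid but answers neither aim by itself.

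Against the interaction, baseline-adjusted ANCOVA at post-test gains about 4 to 15 points for a sustained 0.5 SD effect at correlations 0.3 to 0.7, and nothing from about 0.8. If the effect halves by follow-up, the gain is about 11 to 23 points over correlations 0.3 to 0.8. Whether the effect fades is what the second aim sets out to examine.

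The two-thirds ratio for the main effect needs no assumption beyond randomisation. The power figures rest on the assumed effect size, correlations, 30 per arm and compound symmetry. The change is worth making before the data are analysed, as an improvement to a valid analysis rather than the repair of a biased one.

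**What to change.** In the Statistical analysis section, take baseline out of the within-subjects factor and specify:

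- repeated outcomes: post-test and follow-up;
- terms: group, visit, group-by-visit, and the baseline value of the same scale as covariate;
- primary test: the baseline-adjusted group difference in GDS at post-test, two-sided 0.05;
- second test: the baseline-adjusted group difference in GDS at follow-up, only if the first is significant;
- the same model for SES, LSI-A and UCLA.

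This gives one comparison for each aim, and the fixed order holds the error rate for the primary outcome at 5%. The cost is analysis wording only: no new data, no extra visits and the same software.

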## Discussion

Reminiscence is used as a psychological therapy for depression especially beneficial for elderly adults for the following reasons. First, the reminiscence does not ask for some new complicated skills for elderly, it just employs the resources of them. Therefore it is very suitable for the elderly who decline in cognitive and other functions [8,20]. Secondly, the participants are familiar with their memories. They are the main actors in their stories. It makes them feel comfortable, provides a sense of control and gets them involved in the therapeutic process quickly. Furthermore, it is easier to handle for the therapist than other kinds of intervention, such as cognitive therapy. Though depending on the clinical experience, it still can be used by the graduate student in psychological or nurse who has been trained [41]. Finally, it has been found harmless so far [7].

We also examine whether participants’ attitude and anticipation of the intervention will impact the effect of the intervention. In a research conducted by Arean et al. (1993), participants were requested to anonymously complete a questionnaire about their expectation of the treatment and therapist competency. The finding indicated that subject's perceptions of treatment efficacy, or therapist competency did not influence the outcome measures [28]. However, Bohlmeijer et al. (2009) proposed people who had more positive and general attitude towards reminiscence therapy would benefit more than people who were less interested in that [37]. We will examine these factors in the study. In addition, we will examine the level of participants’ engagement from the therapist’s view to find out whether it will impact the effect of the therapy. This has not been studied in previous studies.

The aim of this study is to evaluate the effects of reminiscence therapy on depression, self-esteem, life satisfaction and loneliness of Chinese elderly. Since the cultures, the values, and the way for expressing of Chinese elderly are different from elderly westerners, it is necessary to verify the applicability of treatment effect of reminiscence into Chinese elderly. Two studies have been conducted in mainland of China [53,54]. However, some methodological shortages limit generalization of the results, such as not RCT design, no well-described protocol and follow-up measurements, which are defined as core characteristics of high quality studies [41]. We will conduct our study following these standards and more strict recruiting criteria to examine whether the reminiscence therapy is effective for Chinese elderly. If the findings of this research are proved to be positive, then we could say it may provide an alternative non-pharmacological therapy that is effective to reduce the depressive symptoms and improve the living quality of potential large older populations in China.

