## Background

Aging population around the world is growing fast. As the United Nations Statistics Division shows, the elderly of the world was about 865 million in 2010, and will reach 2.008 billion in 2050 [1]. Moreover, according to National Bureau of Statistics of China, the Chinese elderly aged 60 and above were about 178 million in 2010, accounting for 13.26% of population [2]. With the increasing number and proportion of the elderly, the geriatric mental health problem becomes more important. Depression is one of the most common mental disorders found in the elderly. In our recent survey of Chinese elderly, the prevalence of self-reported depressive symptoms (CES-D≥16) reached to 39.86% [3]. Depression causes disability of functional impairment, reduces life satisfaction and quality, it is also associated with a high risk of suicidal behavior, and increases the burden and the costs of health and home care services [4-6]. Therefore, the appropriate early intervention for the elderly individual suffering depression is significant and critical [7,8].

At present, drug therapy and psychotherapy are two commonly used methods for the treatment of depression [9]. Depression is mainly treated by medication for a long time [10]. However, previous studies also indicated that pharmacologic approaches had numerous side effects [7,11-13]. In addition, the elderly cannot learn any skills from the drug therapy in protection against the relapse of depression [8]. Currently, increasing studies and reviews support the efficiency of psychotherapeutic treatment for depression. Cognitive or cognitive behavioral therapy [14-16], problem-solving therapy [17] and interpersonal therapy [18,19] are widely accepted as methods in reducing the depression. Based on traditional interventions, reminiscence therapy is specially recommended for geriatric depressive adults. This psychotherapy has been designed and developed because of the recognition of the unique needs and concerns involved in adaptation to the late stage of life [8].

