#### Inclusion criteria

1) The age of participants is equal or over than 60 years old;

2) The score of the Geriatric Depression Scale (GDS) should fall between 10 and 26 points;

3) A score of 24 or higher on the Mini-Mental State Examination (MMSE);

4) Not taking anti-depressant medication or taking part in other psychotherapy when enrolling, or with stable anti-depressant medication for at least three months;

5) Having no problem with communication (such as, can speak fluent mandarin, or, his/her dialect can be understood by other participants or evaluators).

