#### Control group

The participants assigned to the waiting-list as control group will be treated as before. We will keep in touch with them getting to know whether they are still available to be the member of the control group.

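### The conclusion foreseen for a positive result (an 'alternative' to drugs, better 'living quality') goes beyond a pooled waiting-list comparison that includes stable antidepressant users and measures no quality of life

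*Protocol article*

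**What the plan says.** The Abstract and the Background motivate the trial by the drawbacks of drug treatment. The Background says that earlier studies found that "pharmacologic approaches had numerous side effects". The Discussion then looks ahead to a positive finding: "then we could say it may provide an alternative non-pharmacological therapy that is effective to reduce the depressive symptoms". The same sentence goes on to living quality.

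Inclusion criterion 4 accepts people who take no antidepressant and are in no other psychotherapy, "or with stable anti-depressant medication for at least three months". No cap or expected share of users is given. On the comparator, the Control group section says: "The participants assigned to the waiting-list as control group will be treated as before". The Design section words it differently: "the control group participants will not receive any emotional related treatment".

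For the between-group model, the Statistical analysis section says: "The between-subjects factor is group (intervention group, control group" (the quoted bracket closes there). Adjustment is foreseen when the groups differ on demographic data. People who turn to an antidepressant before the end of therapy are excluded from the analysis; those already stable on one at entry stay in.

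The outcomes are the GDS (primary), and self-esteem, life satisfaction and loneliness (secondary).

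**The concern.** Criterion 4 brings two situations into one trial. For a participant on no antidepressant the therapy stands alone; for a stable user it is an addition to a drug. The pooled group effect averages the two, with weights set by whatever mix happens to be recruited.

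The Abstract and Background set the therapy against drug side effects, so many readers will take 'alternative' to mean instead of drugs. Only the non-users bear on whether the therapy works without a drug, and even they are compared with a waiting list, not with a drug. A positive pooled result could therefore be cited for a claim that the trial did not test. 'Living quality' has the same fault on the outcome side: life satisfaction is measured and quality of life is not.

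What is at stake is the meaning of the published conclusion, not the validity of the test.

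**Working it through.** **No figure to reproduce.** The article gives a total of 60 but no power, effect size or SD.

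**Inputs from the article.** Total N is 60 (Participants section). There are two randomised arms, ratio not stated. Tests are two-sided at 0.05 (Statistical analysis). Stable users are eligible, share not stated (criterion 4).

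**Assumptions.** 30 per arm. A share q of participants are stable users. The true benefit is d SD in users and zero in non-users, with SD 1 within each subgroup. The documents give neither q nor d.

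**What the pooled comparison estimates.** Pooled effect = q × d. Because the benefit varies between participants in the therapy arm, the variance there is 1 + q(1−q)d², so

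SE = √[(2 + q(1−q)d²)/30],

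and the chance of a favourable significant result is Φ(q·d/SE − 1.96).

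| q | d in users | Pooled effect | SE | Effect/SE | Chance |
|---|---|---|---|---|---|
| any | 0 | 0 | √(2/30) = 0.258 | 0 | 2.5% |
| 0.2 | 1.0 | 0.20 | √(2.16/30) = 0.268 | 0.75 | 11% |
| 0.5 | 1.0 | 0.50 | √(2.25/30) = 0.274 | 1.83 | 45% |
| 0.2 | 1.5 | 0.30 | √(2.36/30) = 0.280 | 1.07 | 19% |
| 0.5 | 1.5 | 0.75 | √(2.5625/30) = 0.292 | 2.57 | 73% |

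At q = 0.2 the chance stays below 80% however large the benefit in users. At q = 0.5 it reaches 80% only when d is about 1.7. A significant result produced by users alone is possible, but it becomes likely only with a high share of users and a large benefit confined to them.

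**Chance imbalance in antidepressant use.** Take the number of users in each arm as binomial with 30 trials. A difference of at least 6 people (20 percentage points) then has exact probability 7% at q = 0.2 and 15% at q = 0.4. A rule that looks only at demographic data would not pick this up.

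**Precision by baseline use.** The 95% half-width is 1.96 × √(2/n), with n per arm in the stratum. For non-users at q = 0.2, n = 24 and the half-width is 0.57 SD; at q = 0.5, n = 15 and it is 0.72 SD. For users at q = 0.2, n = 6 and it is 1.13 SD.

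**Outcome wording.** The Discussion names depression, self-esteem, life satisfaction and loneliness as what the study evaluates, which matches the outcome sections. 'Living quality' corresponds to none of these scales.

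**The case against.** The strongest reply is that nothing in the aims depends on replacing drugs. The Study purposes section asks whether the therapy improves depressive symptoms compared with control, and the pooled randomised comparison answers that for the people enrolled. The Discussion sentence is hedged, and 'alternative' may mean one more non-drug option beside the cognitive, problem-solving and interpersonal therapies that the Background lists. Subgroup analyses and covariate lists are commonly left to a fuller document that is not shown.

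Much of this stands. A reader might infer that the comparison is biased. It is not: randomisation keeps it valid for the mixed population, and chance imbalance does not change that. A reader might infer that the trial would probably turn positive with no stand-alone effect. The documents give no share of users and no sign of such an interaction, and at 20% users the chance is 11% to 19% in the scenarios above. A reader might also infer that antidepressant use is a strong prognostic factor, or that it is certain never to enter the analysis. The article supports neither. That no analysis by antidepressant use appears in the article is not itself the fault.

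Resting the claim on non-users alone would not rescue it. Their comparator is also a waiting list, and the estimate would be imprecise.

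What the reply does not remove is the gap between a sentence that the article does contain and the eligibility rule, comparator and outcomes that it also contains. The drug side-effect framing makes the stronger sense of 'alternative' the likely one, and the hedging does not tell the reader which population was studied.

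**Conclusion.** The point holds as one of interpretation. The design can support a statement about group reminiscence therapy, alone or added to stable antidepressants, compared with a waiting list. It cannot by itself support an alternative to drugs, and it does not measure quality of life.

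The size depends on two unknowns. With 30 per arm and no benefit in non-users, a favourable significant pooled result has a chance between 11% (20% users, 1.0 SD) and 73% (50% users, 1.5 SD), against 2.5% with no effect in anyone. These figures illustrate the gap and do not predict the result. The wording problem stands without them, because it follows from the passages alone.

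**What to change.** 1. In the Discussion, word the conclusion as: group reminiscence therapy, alone or added to stable antidepressants, compared with a waiting list. Replace 'living quality' by 'life satisfaction'.
2. Include baseline antidepressant use (yes/no) as a prespecified factor in the between-group model, whatever the observed balance. It has to be established anyway to apply criterion 4. The group effect remains the pooled one. The envelopes, which the Design section describes as already prepared, need not be redone.
3. Report the GDS difference between groups with its 95% CI by baseline use, labelled as descriptive only.
4. Reconcile the two descriptions of the control condition (Design and Control group sections) with criterion 4, so that the reader knows what the comparison contains for stable users.

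Cost: one between-subjects degree of freedom, two table rows and a narrower conclusion. The stratum intervals will be wide (half-width about 0.57 SD in non-users at 20% users, 0.72 SD at 50%), which is why they should not carry the conclusion.
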